### Statistical analysis

Congruent with the RCT design of the study, we will conduct an intent-to-treat analysis. We will first use descriptive statistics to check data distribution, identify outliers, guide appropriate data transformation if needed, and summarize sample characteristics. Two-sample *t* tests and Chi-square statistics will be used to check the balance of baseline measures between two study arms. Mixed-effects linear modeling for repeated measures will be used to test the intervention effect on each outcome measure (PMN activation, lipid mediators, inflammatory cytokines, inflammatory cytokine gene expression, percent reduction in wound area, and pain and QoL). In each model, we will include fixed-effects of treatment (EPA + DHA vs. control), time, and treatment by time interaction, adjusting for possible covariates (e.g., lipid-lowering medications) and data dependancy from repeated measures. From the mixed-effects modeling, we will derive the between-group contrast (EPA + DHA vs. control) estimates of change from baseline in outcome variable at each follow-up time point. Multiple comparison adjustment (e.g., Bonferroni adjustment) will be applied to these between-group contrasts to avoid inflated type I error. Logistic regression modeling will be used to analyze wound recurrence. Again, we will estimate between-group difference in the risks of wound recurrence, adjusting for potential covariates and multiple comparison. Lastly, we will use longitudinal mediation modeling [39] to test hypothesized mediating pathways. A significant mediation pathway is indicated if both paths from X (e.g., treatment) to M (mediator, e.g., pro-inflammatory cytokine) and from M to Y (e.g., PMN activation) are statistically significant. Adequate model fit of a mediation model will be indicated with a non-significant Chi-square statistic, comparative fit index, and Tucker & Lewis Index ≥ 0.9, and a root mean square error of appromixation of ≤ 0.08 [40]. The effect of biological sex and its interaction with treatment will also be examined in the regression models. Missing Data. We expect missing data due to non-adherence, loss of follow-up, or lack of data due to healed wounds. We will carefully examine the extent and pattern of missing data. We will use an indicator variable to flag missing data due to healed wounds and incoporate the variable in the missing pattern analysis. Mixed-effects modeling allows for missing at random [41]. If missing completely at random (MCAR) exists, multiple imputation will be used in order to use the optimal amount of information in our analysis. For missing not at random, pattern-mixture modeling will be used [42]. We will also conduct sensitivity analysis to examine the robustness of study findings from different methods. The trial is considered “minimal risk” by the local IRB and therefore no interim analysis or formal plans for stopping the trial are planned. In terms of data and safety monitoring, a Safety Officer (SO) has been selected and approved by the funding agency in consultations with the PI. The SO has no financial, scientific, or other conflict of interest with the trial. The SO meets with the PI twice annually to review study progress, data quality, and participants’ safety.

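### The missing-data rule ties multiple imputation to MCAR and pattern-mixture modelling to a diagnosis of MNAR that observed data cannot supply

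*Protocol article*

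**What the plan says.** All of this is in the protocol article, section Statistical analysis.

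- The main model is fixed without condition: "Mixed-effects linear modeling for repeated measures will be used to test the intervention effect on each outcome measure". The between-group contrasts are to be derived from it, under intent-to-treat.
- Three causes of missing data are foreseen: "We expect missing data due to non-adherence, loss of follow-up, or lack of data due to healed wounds".
- The data are inspected before the methods are assigned: "We will carefully examine the extent and pattern of missing data". For healed wounds, "We will use an indicator variable to flag missing data due to healed wounds"; the flag then enters the missing-pattern analysis.
- The mixed model is described as accommodating MAR. Two further methods are tied to the other mechanisms: "If missing completely at random (MCAR) exists, multiple imputation will be used", for the stated purpose of making the best use of the available information, and "For missing not at random, pattern-mixture modeling will be used".
- A closing sentence promises, without condition, a sensitivity analysis comparing results from different methods. It names neither the methods nor any MNAR assumption.

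**The concern.** The article does not simply leave missing data to a later analysis plan. It states a rule, and the rule has three faults.

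1. **The triggers cannot be observed.** A test can reject MCAR but cannot establish it. MAR and MNAR differ only in how missingness depends on values that were not seen, so no inspection of the pattern can decide between them. The condition for pattern-mixture modelling can be neither met nor ruled out on evidence.
2. **Imputation is placed under the wrong condition.** Standard multiple imputation is justified under MAR. Under MCAR the complete cases are already unbiased and imputation adds at most precision. MCAR is also hard to reconcile with the causes the plan lists, since non-adherence is unlikely to be unrelated to outcome and healing is the outcome.
3. **The status of the extra methods is open.** The text says that they will be used, but not whether they replace the mixed-model result or stand beside it.

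At stake is whether the role of each analysis is settled before the data are seen, and whether the reader is sure to get an analysis that departs from MAR.

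**Working it through.** **The plan's own figure.** The rule carries no number. The nearest figure is the sample size (section Sample size): difference 0.16, SD 0.4, AR(1) correlation 0.7 over three post-baseline measures, two-sided 0.05 with Bonferroni for three comparisons, 80% power, 20% attrition.

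- Variance factor for the mean of three measures: (3 + 2(2 × 0.7 + 0.7²))/9 = 0.753.
- n per arm = 2(z₁₋α/₂ + z₀.₈)² × SD² × 0.753 / 0.16², with α = 0.05/3, gives 99.
- Attrition: 99/0.8 = 123.75, rounded up to 124 per arm, 248 in total.

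The stated 248 is reproduced. Nothing below changes it.

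**Can the mechanism be diagnosed?** This was illustrated with 4,000 simulated trials per mechanism: 124 per arm, true week-12 difference 0.16, SD 0.4, correlation 0.7 between weeks 8 and 12, and about 20% of week-12 values missing. Under MAR, missingness depends on the week-8 value. Under MNAR, it depends on the part of the week-12 value that week 8 does not predict. In both cases poor responders are lost from the EPA + DHA arm and good responders from placebo. The strength of these mechanisms is assumed. The MAR-based estimate uses week 8 to predict week 12. The check compares week-8 values of those with and without week-12 data.

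| Mechanism | Complete cases | MAR-based estimate | Check rejects MCAR |
|---|---|---|---|
| MCAR | 0.162 | 0.161 | 5.3% |
| MAR | 0.260 | 0.159 | 99.8% |
| MNAR | 0.264 | 0.264 | 6.2% |

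- Under MCAR, complete cases are already close to 0.16, so imputation is not needed to remove bias.
- Under MAR, a MAR-based method matters (0.159 against 0.260), yet the rule does not call for imputation there.
- Under this form of MNAR, the check rejects MCAR about as often as when MCAR is true. Such data could be labelled MCAR, sent to imputation and never reach the pattern-mixture step. If MNAR missingness also depended on week 8, the check might reject MCAR, but it still could not tell MNAR from MAR.

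**How far can a departure from MAR move an estimate?** If a fraction 0.20 of week-12 values is missing in the EPA + DHA arm only, and those values differ by δ from what MAR predicts, the estimate is off by 0.20 × δ.

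| δ (points, assumed) | 0.20 × δ | Share of the 16-point target |
|---|---|---|
| 8 | 1.6 | 10% |
| 16 | 3.2 | 20% |
| 24 | 4.8 | 30% |

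The sign follows δ. The 20% is the attrition assumption from the sample-size section, used here as a missing fraction. These figures describe the sensitivity of any MAR analysis, including the mixed model recommended below. They show why a departure-from-MAR analysis is worth guaranteeing; they are not the bias caused by the rule.

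**Healed wounds.** Primary outcome measures defines healing as complete re-epithelialization, so a healed ulcer has area 0 cm² and 100% reduction: known, not missing. Wound fluid collection takes fluid only from unhealed ulcers, so those measures do not exist after healing. Table 1 lists wound area only where a wound is present, and the Missing Data text does not separate the two cases.

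**The case against.** The strongest reply is that the section already contains most of what is needed. The mixed model is named unconditionally, and the sentence about MAR describes a property of that model rather than a branch that selects it. Pattern-mixture modelling is named, and the sensitivity sentence is unconditional and follows directly, so it can naturally be read as covering it. Imputation is valid under MCAR, and its stated aim is information rather than bias removal. Under MAR the likelihood-based mixed model already does the work. Delta ranges and imputation variables normally belong in an analysis plan that is not shown.

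Much of this stands, and it rules out three stronger readings that a reader might infer:

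- **That the main estimate depends on the diagnosed mechanism.** This would follow only if imputation or pattern-mixture results replaced the mixed model, and the text does not say that they do.
- **That MNAR will never be examined.** The named pattern-mixture model and the promised sensitivity analysis do not support this. The fair statement is that such an analysis is not guaranteed.
- **That the area of healed ulcers will be treated as missing.** The text does not say which variables it means.

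The reply does not rescue the triggers. They are stated in the text, and a reader applying them would have to make a judgement the data cannot support. The stated reason for imputing under MCAR applies at least as strongly under MAR. The absence of delta values or an imputation model is not held against the article.

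**Conclusion.** The concern holds in limited form. Multiple imputation is tied to a mechanism that can be rejected but not confirmed, where it is least needed and which the plan's own list of causes makes implausible. Pattern-mixture modelling is tied to a mechanism that observed data cannot distinguish from MAR. The roles of these methods relative to the mixed model are unclear, and an MNAR analysis is not assured.

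The conclusion that the triggers are unusable is a matter of principle and needs no assumed figure. The simulation and the 1.6 to 4.8 point range only illustrate it and rest on assumed mechanisms, an assumed 20% missing fraction and assumed departures. No size can be put on the harm from the rule itself. The correction is worth making because it is cheap and settles the role of each analysis in advance.

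**What to change.** Replace the mechanism-triggered sentences with fixed roles:

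1. The MAR-based mixed model on all observed visits, whatever the softgel adherence, is always the main analysis, in line with intent-to-treat.
2. Any multiple imputation is done under MAR, using auxiliary data already collected: softgel counts and plasma EPA + DHA (Monitoring adherence) and the weekly treatment checks from clinic records (Monitoring clinic wound treatments).
3. A pattern-mixture analysis, for example delta-adjusted, is always reported as the sensitivity analysis, with departures in both directions because people may be missing after doing well or badly.
4. Healed ulcers are handled separately: area is entered as 0 cm² and reduction as 100%, while wound-fluid measures after healing are described as not collectable rather than pooled with loss to follow-up.

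The cost is protocol or SAP wording and one extra analysis run. N stays at 248. The article reports nine participants enrolled, so at that stage the wording could be settled before outcome data accumulated.

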
#### Protocol amendments

The PI will notify the sponsor/funder of this project of any changes to the protocol and will submit the changes for review to the local IRB. The PI will notify the clinical research center (study site) of any protocol changes and will update the protocol in the clinical trial registry.

## Discussion

Chronic venous leg ulcers are wounds that cause substantial morbidity, disability, hospitalization, and even mortality among older adults [3, 4]. New therapies are needed because prevalence rates for CVLUs are rising and standard topical therapies are often ineffective [7, 8, 43]. The high levels and expression of PMN-derived proteases in fluid and tissues biopsied from CVLUs [44–46, 47], and the significantly higher levels of PMN-derived proteases found in chronic wounds compared with healing wounds [48–50] indicate that sustained high levels of PMN-derived proteases are factors in healing delays. There is a body of evidence that the omega-3 fatty acids contained in fish oil (EPA + DHA) mitigate PMN activation [18, 25, 27, 50, 51]. The main goals of this study are to determine the effects of combination therapy with oral EPA + DHA supplementation and standard compression bandaging on PMN activation, CVLU healing, and CVLU recurrence. The findings from this trial are expected to lead to a new low-risk adjunct therapy to target and reduce the excessive PMN activation involved in CVLU pathobiology, stimulate healing, and lessen the negative impact CVLUs have on QoL.

In this study, we have chosen wound area in cm^2^ and PMN activation in systemic circulation and in the wound microenvironment as the primary endpoints. Persistent PMN activation and the resulting high levels of PMN-derived proteases in wound microenvironments are well correlated with slow healing, while lower levels are associated with faster healing [50]. Therefore, this primary outcome measurement is a logical approach to evaluate the effectiveness of oral EPA + DHA therapy to target a specific biological process linked to CVLUs. In addition, we will assess the potential mechanisms of action of the intervention, (EPA + DHA-derived lipid mediators and pro- and anti-inflammatory cytokines) and the secondary endpoints of pain, QoL, and CVLU recurrence.

The omega-3 PUFAs EPA + DHA are metabolized to lipid mediators such as prostaglandin E3 that are weak chemoattractants for PMNs. They also produce the resolvin species that actively slows migration of PMNs to inflammatory sites, triggering inflammation resolution [18, 19]. In vivo experiments in a murine model of peritonitis after zymosam challenge indicated that DHA-derived resolvin D3 reduces PMN transmigration by 45% [52]. Other studies have shown that EPA + DHA-derived lipid mediators slow chemotaxis of PMNs by reducing expression or antagonism of receptors for chemoattractants [53] and by down-regulating gene expression of pro-inflammatory cytokines that signal PMN activation [27]. The studies by these groups were well designed and executed, but there is a need to determine the extent that EPA + DHA therapy increases EPA + DHA-derived lipid mediators and reduces pro-inflammatory cytokine synthesis in more in vivo studies of humans with conditions such as CVLUs linked to excessive PMN activation, versus cell and animal models of inflammation. There is also a need to determine effects of EPA + DHA therapy on omega-6 PUFA-derived lipid mediators. The n-3 and n-6 PUFA families are competitively metabolized and n-6 PUFAs such as arachidonic acid generate lipid mediators that are strong chemoattractants for PMNs (e.g., leukotriene B4) and signal gene expression of pro-inflammatory cytokines in cells [20, 54].

At the end of this trial, we expect to know the extent that EPA + DHA therapy and the proposed mediating factors reduce PMN activation, expedite CVLU healing, and prevent recurrence. We expect to know more about the mechanisms of action of EPA + DHA therapy and its subsequent impact on ulcer pain and QoL. This knowledge will propel us toward our long-term goal *–* to help prevent or facilitate healing of CVLUs in aging and thereby improve QoL. After this study, next steps may include (1) a pragmatic trial to test EPA + DHA therapy in the everyday clinical setting to maximize generalizability, assess cost effectiveness, and determine the feasibility of using a point-of-care test [55] that can measure protease levels in CVLU fluid within minutes, (2) determining the extent that EPA + DHA therapy prevents CVLUs in people with known venous disease, and (3) determining the extent that genetic factors affect EPA + DHA metabolism. We predict that EPA + DHA oral therapy added to standard topical care will greatly improve CVLU healing outcomes and as such, reduce the substantial emotional and financial burdens caused by these serious wounds in aging (Additional file 1).

## Trial status

Protocol version #3, April 24, 2019. Registered at Clinicaltrials.gov, identifier: NCT03576989. Currently recruiting, with nine participants enrolled. Trial start date was April 15, 2019. Anticipated recruitment end date is March 15, 2023.

## Data Availability

Information and datasets gathered as a result of this trial will be available from the corresponding author upon reasonable request. Results and findings of the study will be released through publications in scientific literature and conference presentations.

## Abbreviations

ABPI: Ankle brachial pressure index
CRC: Clinical research center
CVLU: Chronic venous leg ulcer
CWC: Comprehensive wound center
DHA: Docosahexaenoic acid
EPA: Eicosapentaenoic acid
HbA1c: Hemoglobin A1c
MCAR: Missing completely at random
n-3: Omega 3
n-6: Omega 6
OSU: Ohio State University
PI: Primary investigator
PMN: Polymorphonuclear leukocytes
PUFA: Polyunsaturated fatty acids
QoL: Quality of life
SO: Safety officer
VCSS: Venous Clinical Severity Score
VEINES-QOL/Sym: Venous Insufficiency Epidemiological and Economic Study-Quality of Life/Symptoms
